### Statistical analysis

Data analysis on the final dataset will be performed using SPSS statistical software. The per-protocol principle will be used since patients who withdraw consent before the ablation has taken place are excluded from the analysis. Univariate analysis will be applied to both continuous (*t* test or nonparametric tests) and categorical variables (Chi-square test). Continuous variables will be reported as the mean ± standard deviation (for normally distributed variables) or median/p10–p90 (for not normally distributed variables), and categorical variables will be reported as the observed number and corresponding percentage. Depending on the number of events, univariate (*t* test or Chi-square) or multivariate analysis (logistic regression) will be used to explore the relationship between baseline covariates and post-baseline endpoints. Kaplan-Meier survival curves will be plotted. All necessary decisions with regards to power calculations for secondary endpoints are made blind. Missing data are not computed or imputed, and the participant will be excluded for the analysis which involves the missing data.

For the cost-effectiveness analysis, any missing data will be imputed using a multiple imputation approach. As most volumes of resource use follow a skewed distribution, differences between the two groups will be analyzed with bias-corrected bootstrap analysis. In addition, bootstrap analysis will also be used to quantify the uncertainty surrounding the incremental cost-effectiveness ratio. Results of this analysis will be presented in cost-effectiveness planes and acceptability curves. Sensitivity analysis will be performed to estimate, for example, the impact of parameters on the incremental cost-effectiveness ratio. Discounting will be applied for both costs (4%) and effects (1.5%).

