## Methods

### Design and hypothesis

This is a prospective, randomized trial conducted at the Maastricht University Medical Centre, Maastricht, the Netherlands. The study objective is to compare the efficacy and safety of two interventional approaches for symptomatic, drug refractory persistent or longstanding persistent AF. A total of 40 eligible patients will be randomized (in a 1:1 ratio) to the following treatment arms: 1) a hybrid ablation arm (*n* = 20 patients), a one-stage hybrid procedure consisting of surgical thoracoscopic epicardial ablation combined with endocardial catheter ablation; or 2) a catheter ablation arm (*n* = 20 patients), consisting of conventional endocardial catheter ablation, followed by repeated catheter ablation if clinically indicated and decided within 6 months after the initial procedure.

The primary and secondary effectiveness endpoints are shown in Table 1. A blanking period of 3 months is applied. A second ablation after the hybrid ablation and a decision for redo-ablation beyond 180 days after the index catheter ablation will be considered a failure. A third catheter ablation at any time will also be considered a failure in the catheter arm. While the current guidelines define failure as a recurrence of > 30 s, failure in the primary endpoint of this study is defined as a recurrence of > 5 min [19, 21]. This allows us to reliably evaluate various Holter examinations and this reflects a more clinical endpoint compared with > 30 s, since it has been shown that the presence of AF episodes >30 s do not predict clinically meaningful AF, and that quality of life is mainly negatively influenced in patients with a high symptomatic AF burden [22, 23]. The primary and secondary safety endpoints are shown in Table 2.

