### Randomization

Randomization will be performed directly after written informed consent is obtained by the Clinical Trial Center Maastricht using the ALEA software program (FormsVision BV, Abcoude, the Netherlands). This software is programmed to equally distribute the number of patients over the two groups so that an even number of patients are treated with either catheter or hybrid ablation. The randomization is block designed and restricted (stratified); the type of AF (persistent or longstanding AF) will be taken into account to ensure a good balance of patient characteristics in both groups. Using this randomization method, allocation concealment is guaranteed. For every patient that withdraws their consent before the ablation is performed, an additional patient will be randomized.

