### Pre-procedural investigations

Pre-procedural investigations include physical examination, 12-lead electrocardiogram (ECG), blood analysis (e.g., hemoglobin, C-reactive protein, creatinine), transthoracic echocardiography, a lung function test, and a standard computed tomography (CT) scan. Patients older than 60 years and patients with an elevated cardiovascular risk profile (i.e., family history of cardiovascular disease, elevated body mass index, diabetes, dyslipidemia, hypertension, or smoking) will undergo a cardiac CT scan or coronary angiogram. In addition, quality of life (using the EQ-5D-5 L questionnaire) is assessed at baseline.

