### Cost-effectiveness

The economic evaluation will examine the cost-effectiveness of hybrid AF ablation compared with (repeated) transvenous endocardial catheter ablation from a societal perspective with a time horizon up to 36 months. The outcome measure will be the incremental costs per quality-adjusted life year (QALY) gained. To calculate the QALY, a generic health-related quality of life questionnaire, the EQ-5D-5 L, will be administered at baseline and at 12 and 36 months. The Netherlands tariff will be used to value the health states as experienced by patients [25].

All resource use related to both procedures within the hospital will be recorded. In addition, medical consumption of patients during follow-up will be recorded using the iMCQ, while productivity loss will be obtained using the iPCQ [26, 27]. For the valuation of resource use, unit prices will be derived from the Pharmacotherapeutic Compass, the Netherlands guidelines for cost calculation [28], and the hospital financial department.

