### Sample size calculation

The estimated success rate (freedom from any supraventricular arrhythmia lasting > 5 min without the use of Vaughan-Williams class I or III AAD through 12 months of follow-up after the last procedure) based on literature and our own clinical experience is 35% for single catheter ablation [2, 29] and 83% for a hybrid ablation [30, 31]. With a significance level of α = 0.05, and a power of 90%, 20 patients per group need to be included.

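### The stated t test or nonparametric test leaves the baseline EQ-5D-5L unused: the comparison stays valid, but ANCOVA would give more precision with 20 patients per arm

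*Protocol article*

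**What the plan says.** All places are in the Methods of the protocol article.

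- **Collection.** Under Pre-procedural investigations, "quality of life (using the EQ-5D-5 L questionnaire) is assessed at baseline". Under Cost-effectiveness the questionnaire "will be administered at baseline and at 12 and 36 months", for the calculation of QALYs.
- **Continuous variables.** Statistical analysis says: "Univariate analysis will be applied to both continuous (*t* test or nonparametric tests". It does not say whether the tested value is the follow-up score or the change from baseline.
- **Baseline covariates.** Their only stated use is exploratory. The one multivariable method named is logistic regression, conditional on the number of events, which does not suit a utility score.
- **Economic evaluation.** The bootstrap of group differences is introduced for skewed resource use. For the cost per QALY, "bootstrap analysis will also be used to quantify the uncertainty surrounding the incremental cost-effectiveness ratio". No covariate is named. Multiple imputation and discounting of effects at 1.5% are stated.
- **Size and balance.** "A total of 40 eligible patients will be randomized (in a 1:1 ratio) to the following treatment arms", with 20 patients in each. Under Randomization, "the type of AF (persistent or longstanding AF) will be taken into account to ensure a good balance of patient characteristics"; no other factor is named, so baseline utility is left to chance.

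**The concern.** Quality of life and cost per QALY are outcomes of this trial, and its size was set for a binary rhythm endpoint. With 20 patients per arm, the precision left for a utility score is scarce. The baseline value of the same score often predicts the follow-up value, and it is already scheduled for collection. A two-sample test on follow-up values discards that information.

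The QALY comparison has the same exposure in a more direct form. If QALYs are the area under the utility curve, baseline utility is part of the total, and it is also correlated with the later values. Without adjustment, a chance difference between arms at baseline carries into the incremental QALYs and widens their uncertainty.

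**Working it through.** **The plan's own figure.** The Sample size calculation section assumes success in 35% of patients after one catheter procedure and in 83% after the hybrid procedure, sets α at 0.05 and power at 90%, and arrives at 20 per arm. Two-sided, pooled variance under the null, no continuity correction:

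n = [1.96·√(2·0.59·0.41) + 1.2816·√(0.35·0.65 + 0.83·0.17)]² / 0.48² = (1.363 + 0.778)² / 0.2304 ≈ 19.9, so 20 per arm.

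It reproduces. It concerns the primary endpoint and is not affected by what follows.

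**EQ-5D-5L at one follow-up visit.** Inputs: n = 20 per arm (documents); two-sided 0.05 (sidedness assumed); standardised difference d and baseline-to-follow-up correlation ρ (assumed, as the documents give neither). Power is from the noncentral t distribution with noncentrality d / √(f·2/20).

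- t test on follow-up values: f = 1, 38 df
- t test on change scores: f = 2(1 − ρ), 38 df
- ANCOVA on baseline: f = (1 − ρ²)(1 + 1/36), 37 df

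For d = 0.8:

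| ρ | t test, follow-up | t test, change | ANCOVA |
|---|---|---|---|
| 0.3 | 69.3% | 54.9% | 72.2% |
| 0.5 | 69.3% | 69.3% | 80.1% |
| 0.7 | 69.3% | 88.9% | 92.5% |

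Example at ρ = 0.5: f = 0.75 × 1.028 = 0.771; noncentrality 0.8 / √(0.771 × 0.1) = 2.88; power 80.1%.

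Smaller effects at ρ = 0.5: d = 0.4 gives 23.4% against 28.9%; d = 0.25 gives 12.0% against 14.2%. At ρ = 0 and d = 0.8, ANCOVA has 68.1% against 69.3%, a loss of about 1 point. A second covariate that explained nothing, f = (1 − ρ²)(1 + 2/35) with 36 df, would cost about 1 further point (79.0% instead of 80.1% at ρ = 0.5).

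**QALYs to 36 months.** Assumptions: trapezoid through 0, 1 and 3 years, utility SD 0.2 at each time, equal correlation ρ between times, no discounting. The weights are 0.5, 1.5 and 1.0 years.

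- SE of the chance difference in mean baseline utility: 0.2·√(2/20) = 0.063. A difference of at least 0.05 in either direction then has probability 2[1 − Φ(0.05/0.063)] = 0.43.
- Slope of QALY on baseline utility: b = 0.5 + 2.5ρ. A baseline difference of 0.05 goes with a shift of 0.05b in the unadjusted incremental QALYs.
- QALY variance in units of SD²: V = 0.5² + 1.5² + 1.0² + 2ρ(0.75 + 0.5 + 1.5) = 3.5 + 5.5ρ.
- SE unadjusted = 0.2·√(V/10); SE adjusted = 0.2·√((V − b²)/10).

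| ρ | b | V | shift for 0.05 | SE unadjusted | SE adjusted |
|---|---|---|---|---|---|
| 0.3 | 1.25 | 5.15 | 0.0625 | 0.144 | 0.120 |
| 0.5 | 1.75 | 6.25 | 0.0875 | 0.158 | 0.113 |
| 0.7 | 2.25 | 7.35 | 0.1125 | 0.171 | 0.096 |

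The adjusted SEs leave out the small-sample factor √(1 + 1/36) ≈ 1.014, which does not alter the picture.

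**The case against.** **The sentence on continuous variables is generic.** It names neither EQ-5D-5L nor the form of the variable, and a change score would use the baseline. That is fair, and at ρ = 0.7 change scores come within 4 points of ANCOVA. At ρ = 0.5 they only match the plain t test, and at ρ = 0.3 they do much worse. ANCOVA has more power than either at all three correlations, so the ambiguity does not remove the point.

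**A reader might infer that the plan fixes an unadjusted QALY comparison.** It does not. The bootstrap of group differences concerns resource use, the bootstrap of the cost-effectiveness ratio concerns uncertainty only, and a bootstrap can be combined with regression. This is also a condensed article, and the full protocol or analysis plan may name the covariates. The QALY part is therefore a recommended addition and not an error in the text.

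**A reader might infer that imbalance biases the incremental QALYs.** Under randomization it is chance error and already lies inside the bootstrap uncertainty. At ρ = 0.5 the shift for a 0.05 imbalance is 0.0875 / 0.158 = 0.55 of the unadjusted SE. The documents give no expected QALY gain, so they cannot show that such a shift would change the cost-effectiveness conclusion.

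**The gain may be small.** This stands for low correlations and small effects. A d of 0.8 at SD 0.2 is a utility difference of 0.16, which is large.

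**Conclusion.** The point holds as one of efficiency. For EQ-5D-5L at 12 and 36 months the stated univariate test is valid but less precise than the collected data allow, and a better method is available at almost no cost. The size depends on a correlation that the documents do not give. At d = 0.8 the gain over a t test on follow-up values is about 3 points of power at ρ = 0.3, 11 at 0.5 and 23 at 0.7. At d = 0.25 and ρ = 0.5 it is about 2 points.

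For QALYs, under the assumptions listed, adjustment would cut the SE by about 17%, 29% and 44% (1 − 0.120/0.144, 1 − 0.113/0.158, 1 − 0.096/0.171). The documents do not support reading this as a stated flaw in the economic analysis, as systematic bias, or as a threat to the primary result.

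**What to change.** In Statistical analysis:

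1. Compare EQ-5D-5L at 12 and at 36 months by ANCOVA on arm, baseline EQ-5D-5L and AF type (the stratification factor). Report the adjusted difference with its 95% CI, bootstrapped if the scores are skewed.
2. In the economic evaluation, estimate incremental QALYs by regressing QALYs on arm and baseline utility within each bootstrap replicate and each imputed dataset. Build the cost-effectiveness ratio, planes and acceptability curves from these increments, and keep the unadjusted result as a sensitivity analysis.
3. Use as covariate the pre-procedural EQ-5D-5L already collected, and state whether it was completed before the patient learned the allocation. Randomization directly follows consent and treatment is not masked from the patient; the text does not place the baseline questionnaire before allocation, and the SPIRIT figure could not be read here.

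The cost is one or two sentences and a few lines of code, with no new visits or patients. Each covariate takes one degree of freedom, about 1 point of power if it predicts nothing. Fixing the model before the data are seen also prevents choosing adjustment after an imbalance is visible.

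### Randomisation is stratified by AF type, but the only between-arm test stated for categorical outcomes ignores the strata: a minor loss, and only if AF type is strongly prognostic

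*Protocol article*

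**What the plan says.** Under Randomization, the article states "The randomization is block designed and restricted (stratified" and names one factor with two levels: "the type of AF (persistent or longstanding AF) will be taken into account to ensure a good balance of patient characteristics in both groups".

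Under Statistical analysis, univariate comparisons are planned, with a chi-square test for categorical data ("categorical variables (Chi-square test"). No strata are mentioned. Regression enters only subject to how many events there are, and for another purpose: "multivariate analysis (logistic regression) will be used to explore the relationship between baseline covariates and post-baseline endpoints". AF type is not named there. Kaplan-Meier curves are to be plotted, with no test attached.

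The primary effectiveness endpoint, arrhythmia-free without class I or III drugs through 12 months, is binary. Under Sample size calculation the assumed success rate "is 35% for single catheter ablation [2, 29] and 83% for a hybrid ablation [30, 31", and "With a significance level of α = 0.05, and a power of 90%, 20 patients per group need to be included".

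**The concern.** Blocking within strata forces the arms to have nearly the same mix of AF types. If AF type predicts outcome, this removes part of the random variation in the difference between arms. An unstratified chi-square still counts that part in its variance. It then rejects too seldom under the null, and its confidence interval is wider than it need be. At stake is efficiency in a trial of 40 patients, not bias and not an inflated false-positive rate.

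There is also a point of prespecification. Whether any covariate-adjusted model is used depends on the number of events, so the plan leaves open how far AF type will enter the analysis until data are in.

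**Working it through.** **1. The plan's own figure.** Inputs from Sample size calculation: p1 = 0.35, p2 = 0.83, α = 0.05 (taken as two-sided; the article does not say), power 0.90. The mean rate is 0.59.

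n per group = [1.960·√(2·0.59·0.41) + 1.2816·√(0.35·0.65 + 0.83·0.17)]² / 0.48²
= [1.960·0.6956 + 1.2816·0.6071]² / 0.2304
= 2.1413² / 0.2304 = 19.9, so 20.

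The stated 20 per group is reproduced, with 90.2% power by the normal approximation and 89.7% by exact calculation. It matches an unstratified test of two proportions without continuity correction.

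**2. Likely strata.** The Discussion describes 70 initial catheter ablations at the centre, 60 in persistent and 10 in longstanding persistent AF. For an arm of 20, 20 × 60/70 = 17.1, so about 17:3. An even 10:10 mix is taken as the other bound.

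**3. Mechanism.** Let a share w of each arm lie in stratum A, with common success rates pA and pB under the null. The chi-square uses a per-patient variance p̄(1 − p̄). With exact balance the relevant variance is w·pA(1 − pA) + (1 − w)·pB(1 − pB). The excess is w(1 − w)(pA − pB)².

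- 17:3, rates 45%/25%: 0.85 × 0.15 × 0.20² = 0.0051 out of 0.2436, about 2%.
- 17:3, rates 55%/15%: 0.85 × 0.15 × 0.40² = 0.0204 out of 0.2499, about 8%.
- 10:10, rates 55%/15%: 0.5 × 0.5 × 0.40² = 0.0400 out of 0.2275, about 18%.

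The excess grows with the square of the gap and is small when one stratum is small.

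**4. Size at nominal 5%.** 20 per arm, exact 1:1 split within strata, Pearson chi-square against CMH = [Σ(a_k − E_k)]²/ΣV_k without continuity correction. Here a_k is the number of successes in one arm of stratum k, E_k and V_k are its hypergeometric mean and variance, and V_k = m_k(2n_k − m_k)/[4(2n_k − 1)] for m_k successes and n_k patients per arm. Probabilities are summed over all possible tables; simulations of 400,000 trials agree. The stratum rates are assumptions.

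| Success in strata | 17:3 crude / CMH | 10:10 crude / CMH |
|---|---|---|
| 35% / 35% | 5.2% / 4.7% | 5.2% / 4.6% |
| 40% / 30% | 4.9% / 4.6% | 5.1% / 4.7% |
| 45% / 25% | 4.4% / 4.6% | 4.7% / 4.9% |
| 55% / 15% | 3.4% / 4.9% | 3.3% / 4.9% |
| 70% / 30% | 4.1% / 4.9% | 2.6% / 4.8% |
| 65% / 20% | 3.5% / 4.9% | 2.5% / 4.9% |
| 80% / 30% | 3.4% / 5.0% | 1.9% / 4.9% |

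Not every shortfall comes from stratification. With a common 43% in both strata the crude size is already 4.6%, and with a common 50% it is 4.25%, because the counts are small and discrete.

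**5. Power at 17:3, crude against CMH.**

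| Scenario | Crude | CMH |
|---|---|---|
| 35% vs 83%, no AF-type effect | 89.7% | 89.0% |
| 35% vs 83%, AF-type odds ratio 2.7 | 90.0% | 90.0% |
| 35% vs 83%, odds ratio 7.4 | 90.8% | 92.5% |
| 35% vs 83%, odds ratio 20 | 91.9% | 94.8% |
| 43% vs 83%, no AF-type effect | 77.8% | 76.2% |
| 63%/23% vs 95%/71% by stratum | 75.3% | 78.1% |

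The 43% is the centre's drug-free success after a redo procedure (Discussion), used here as an alternative control rate. The differences run from −1.6 to +2.9 points. At 10:10 the last scenario gives 79.3% against 83.4%.

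**The case against.** The strongest reply has four parts.

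- The chi-square sentence is generic. It neither names the primary endpoint nor assigns a confirmatory test, and a full protocol or SAP may specify a stratified one. This stands as a limit on what can be claimed. Still, the article does state a univariate test next to a stratified design, and its sample size matches that test. The point therefore concerns a stated choice, not only a missing detail.
- A reader might infer that AF type was chosen because it is known to be prognostic, and that the chi-square is therefore conservative in this trial. The documents support neither step. The reason given for stratifying is balance of patient characteristics, and no success rate by AF type appears anywhere. With gaps of 20 points or less the test is close to nominal.
- Exact balance within strata is the worst case. With random stratum sizes (one seventh longstanding) and permuted blocks of four (an assumed block size), crude against CMH size was 4.5% against 4.7% at 45%/25%, 4.3% against 4.9% at 70%/30%, and 3.9% against 4.9% at 65%/20%. This stands and narrows the effect further.
- The gain in power is small at the centre's own mix and turns into a small loss if AF type does not matter. This also stands.

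What remains is a mismatch between design and stated analysis that errs on the safe side and costs almost nothing to remove.

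**Conclusion.** The point holds as a minor one. Randomisation uses AF type; the stated test for categorical outcomes does not; and the regression that might use it is exploratory and conditional. The crude test is valid. Under exact balance and a gap of 40 to 50 points between strata, its size is about 3.4-4.1% at 17:3 and 1.9-3.3% at 10:10, against about 4.8-5.0% for CMH. In the tabulated scenarios with a gap of 20 points or less it is 4.4-5.2%, which is near nominal.

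These figures rest on assumed success rates by AF type, on a stratum mix borrowed from the centre's earlier series, and on exact within-stratum balance. They do not show that the trial's test is in fact conservative, that its false-positive rate is at risk, or that 20 per group is wrong for the rates stated.

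**What to change.** State in advance that the primary comparison is a Cochran-Mantel-Haenszel test stratified by AF type as recorded at randomisation. Report the Mantel-Haenszel risk difference with a 95% CI, and show the crude chi-square as a supporting result. Do not let use of the stratified analysis depend on the number of events.

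Say explicitly that no continuity correction is applied, and check which version the software prints. With the correction, the size in the simulated scenarios falls to about 1.5-2.1%, and power at 35% vs 83% with no AF-type effect falls to about 81%.

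Cost: a sentence or two of analysis text, best fixed before results are seen. AF type is already collected and the sample size stays at 20 per group. The downside is about 1 to 2 points of power if AF type has no prognostic value.

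### The exploratory tests of baseline covariates may drop randomised arm when events are few; arm should stay in every covariate analysis

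*Protocol article*

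**What the plan says.** The Statistical analysis section of the Protocol article gives two routes for relating baseline covariates to later endpoints. The choice between them is made by event count: "Depending on the number of events, univariate" tests (t test or Chi-square) are one route, and the other is "multivariate analysis (logistic regression) will be used to explore the relationship between baseline covariates and post-baseline endpoints". No event threshold is given. The text does not say whether the univariate tests combine the arms, and it does not list the terms of the logistic model.

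The Sample size calculation section says the assumed success rate "is 35% for single catheter ablation [2, 29] and 83% for a hybrid ablation", and concludes: "With a significance level of α = 0.05, and a power of 90%, 20 patients per group need to be included". Under Randomization, allocation is stratified, so that "the type of AF (persistent or longstanding AF) will be taken into account to ensure a good balance".

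**The concern.** A t test or Chi-square test of one covariate against one endpoint has no place for a second factor. If patients from both arms go into it together, the planned 48-point difference in success is ignored. Two things follow. Where a covariate is unequal between arms, part of the treatment effect is credited to it or set against it. Where it is equal, the arm difference inflates the variance that the test uses, and the test becomes conservative.

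The event-count rule also works in an awkward direction. Few events lead away from the only named method that could hold arm. What is at stake is the reliability of any statement about which patients do well after ablation. The comparison of hybrid with catheter ablation is not at stake.

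**Working it through.** **1. The plan's own figure.** Inputs: success 0.35 and 0.83, two-sided α = 0.05 (sidedness is not stated; two-sided reproduces the figure), power 90%.

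n = [1.96 × √(2 × 0.59 × 0.41) + 1.2816 × √(0.35 × 0.65 + 0.83 × 0.17)]² / 0.48² = [1.363 + 0.778]² / 0.2304 = 19.9, so 20 per arm. Power at 20 per arm is 90.2%. The stated figure reproduces.

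**2. Is the univariate route realistic?** Expected failures on the primary endpoint are 20 × 0.65 + 20 × 0.17 = 13 + 3.4 = 16.4. That supports one or two model terms, so the univariate route could well be taken.

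**3. How far imbalance shifts a covariate with no effect.** Assume a binary covariate present in 20 of the 40 patients, with d more carriers in one arm than in the other. The expected difference in failure rate between carriers and non-carriers is d × 0.48 / 20:
- 12 v 8 (d = 4): 9.6 points
- 13 v 7 (d = 6): 14.4 points
- 14 v 6 (d = 8): 19.2 points

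**4. Size by normal approximation.** The combined test uses a standard error of √(0.41 × 0.59 × 2/20) = 0.156. The actual standard deviation, given the arms, is √[(20 × 0.2275 + 20 × 0.1411)/400] = 0.136. With d = 0, size is P(|Z| > 1.96 × 0.1555/0.1358) = P(|Z| > 2.245) = 2.5%. Adding the shifts above gives 6.4%, 11.9% and 20.3%.

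**5. Size by simulation** (20 per arm, failure 65% v 17%, Pearson Chi-square on both arms together against a Cochran-Mantel-Haenszel test stratified by arm, 5% level):

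| Split between arms | Arms combined | Stratified by arm |
|---|---|---|
| 10 v 10 | about 2% | 4–5% |
| 12 v 8 | about 6% | about 5% |
| 13 v 7 | about 11% | about 5% |
| 14 v 6 | about 19% | about 5% |
| Average over randomisations | about 5% | about 5% |

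**6. How often imbalance occurs.** With 50% prevalence, the difference between two independent Binomial(20, 0.5) counts is distributed as Binomial(40, 0.5) − 20. It reaches 4 or more in either direction with probability 26.8%, and 6 or more with probability 8.1%.

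**7. Power for a true predictor.** Intercepts are set so that each arm keeps its planned rate. Averaged over randomisations:

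| Odds ratio | Arms combined | Stratified by arm | Loss |
|---|---|---|---|
| 4 | 34% | 41% | 7 points |
| 6 | 48% | 59% | 11 points |
| 8 | 58% | 70% | 12 points |

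At a fixed 12 v 8 split and odds ratio 6, the direction matters. With the imbalance working against the predictor, power is 21% combined and 58% stratified. With the imbalance working for it, power is 75% combined and 59% stratified.

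**8. The other reading, separate tests within each arm.** With a balanced covariate and odds ratio 6, power is 39% in the catheter arm and 17% in the hybrid arm. The corresponding figures are 46% with arms combined and 61% stratified.

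**The case against.** The strongest reply is that the defect is inferred. A reader might take the section to prescribe combined tests that leave out arm, but it says neither. The tests could be run within arms, and the logistic model could include arm. Model terms for an exploratory analysis are also commonly left to a full protocol or analysis plan, which is not shown. This stands against any claim that the article specifies a wrong model. It does not remove the point, because the univariate tests are named as the method and cannot hold arm, and the within-arm reading also loses power (step 8).

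A second stronger reading is that chance imbalance will commonly produce false predictors. The figures do not support it. A difference of 4 or more is common (27%), but at 12 v 8 the size is only about 6%. Marked inflation starts at 13 v 7, and average size stays near 5%.

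A third is that real predictors will be missed because arm is left out. They would be missed somewhat more often, but the main limit is 40 patients: with arm included, power is still only 41% at odds ratio 4. The bias at a given imbalance also runs both ways.

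Three further points stand. The section already frames the analysis as one to "explore the relationship between baseline covariates and post-baseline endpoints". AF type is approximately balanced by the stratified randomisation, so the risk of inflation hardly applies to it; for a balanced covariate the cost is conservatism. And no stated aim of the trial depends on this analysis.

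**Conclusion.** The point holds as a minor, conditional one. The plan permits univariate tests that cannot account for arm, and about 16 expected failures make that route plausible. If the arms are combined, the test is conservative for balanced covariates (about 2% size) and clearly inflated only at marked imbalance (about 11% at 13 v 7, 19% at 14 v 6; a difference of 6 or more in about 8% of randomisations). It loses about 7 to 12 points of average power at odds ratios of 4 to 8.

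These figures assume a binary covariate with 50% prevalence and the planned success rates; the article gives no covariate prevalence or odds ratio. They scale with the arm difference. The 35% is for a single catheter ablation, whereas the arm allows a second. If catheter success were 43%, the centre's own rate after redo without antiarrhythmic drugs (Discussion), the shift at 13 v 7 would be 6 × 0.40/20 = 12.0 points, not 14.4. For endpoints with little difference between arms, the problem largely disappears. The primary arm comparison is not affected.

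**What to change.** State that randomised arm is kept in every analysis of baseline covariates against post-baseline endpoints. Either use logistic regression with arm plus one covariate at a time, or use a Mantel-Haenszel test (for continuous variables, a linear model) stratified by arm. Let the number of events decide only whether further covariates are added.

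The cost is one sentence in the Statistical analysis section, little extra work in SPSS, and one degree of freedom per model. No additional patients or data are needed. The change will not make the predictor analysis well powered; it removes an avoidable loss and a dependence on chance imbalance.
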